#### Power calculation

4.7.1

As the approach of this study is biopsychological, we drew on selected data from different domains from relevant studies to estimate effect sizes: metabolic differences between active smokers and former smokers, changes in gut microbiome parameters, and a psychological variable during smoking cessation. A recent multi-omics study (27) compared metabolite levels between cigarette smokers, e-vapers, and former smokers. N-acetylputrescine metabolite concentrations showed a clear association with smoking-related metabolic variation. Because raw metabolite concentrations were not given, effect sizes of standardized differences between cigarette smokers and former smokers were estimated from the correlation between N-acetylputrescine and the combustion-related principal component (PC1), giving an estimated approximate standardized mean difference of Cohen’s d ≈ 0.73, indicating a medium-to-large effect size. This suggests substantially higher N-acetylputrescine levels in cigarette smokers compared with former smokers, consistent with persistent alterations in polyamine metabolism in active smoking.

For microbiome changes after smoking cessation, Sublette et al. (67) reported increased abundances of Bacteroidetes in successful abstainers (n=14 of 26 at week 12). The increase in relative abundance of Bacteroidetes from baseline to 12 weeks in smokers who quit compared with those who continued smoking corresponded to an approximate standardized effect size of r ≈ 0.41 (based on regression estimate β = 7.4 percentage points, SE = 3.5), suggesting a moderate effect.

Psychological self-efficacy increased during smoking cessation in a pilot study by our own research group (55) and showed a medium-to-strong effect (η_p_^2^ = .11; converted to Cohen’s d ≈.70).

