A-priori sample size calculations were performed with G-Power (108) (version 3.1.9.6), for a mixed-design ANOVA with one interaction between group (2 groups) and assessments (2 repeated measurements). Considering the effects mentioned above, the mixed-design ANOVA was set rather conservatively for a medium effect size (Cohen’s F = 0.25), a statistical Power (1-β) of 0.9, a α of 0.05, an intra-correlation coefficient of 0.5 and nonsphericity correction of 1, resulting in a minimum sample size of 46 subjects per group, and a critical F = 4.06. Adjusting for expected attrition of about 10%, a total sample size of size of 100 is set. The many (mostly biological) variables measured in this study will expectably require statistical corrections; this will also be compensated by statistical methods exceeding classical linear approaches, namely machine learning feature detection and modelling methods (109).

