#### Controlling for potentially confounding variables, and multiple testing

4.7.3

Proper analysis of the research questions in the SUD sample will be hampered by several sources of variance, such as diet, psychiatric diagnoses, medications, and history of substance misuse. These variables will be held constant as control variables.

Psychiatric comorbidity is highly present in the population. Psychiatric symptom burden and classes of psychiatric diagnoses are associated with systematic metabolic and microbiome profiles (72, 113, 114). Classes of psychiatric secondary diagnoses (mood, anxiety, psychotic, and neurodevelopmental disorders) will therefore be considered as covariates. Intake of psychotropic medications are respectively frequent. The literature shows reciprocal interactions between psychotropic medications and gut microbiota (115), and metabolic patterns in response to treatment (116, 117). Type of medication class intake (antipsychotics, antidepressants, antianxiety drugs, anticonvulsants/mood stabilisers, opioid substitution) will be considered as covariates. Length and consumption patterns from SUD history will also enter covariate analysis (with regard to substances – primarily consumed substances vs. polytoxicomania). These covariates will be entered in Multi-omics factor analysis (MOFA) in direct joint modeling (118) to ensure that observed microbiome–metabolome–psychological associations are not driven by covariate effects. For the microbiome domain, intervention vs. control group comparisons regarding microbial abundance and composition will be performed with Analysis of Compositions of Microbiomes with Bias Correction (ANCOM-BC), a package which allows for continuous and categorical covariate adjustment within a linear regression framework, and was designed to analyze longitudinal data (119).

Metabolome and microbiome studies involve the examination and statistical testing of a multitude of variables. Thus, controlling for multiple testing is a must; False Discovery Rate corrections will be based on statistical recommendations promoting flexible algorithms within the R package FDRestimation (120).

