#### Statistical analyses of psychological variables

4.7.4

The statistical analyses will be performed in SPSS version 29 (IBM) for general procedures, while specific regression models are handled in R (R core team (121)). For example, t-tests will be carried out for independent and paired comparisons of means between and within groups at different times, respectively, assuming that the continuous data are normally distributed. Chi-square and Fisher’s exact tests, the latter in cases of smaller sample sizes, will be conducted in order to test the associations between categorical variables. The Friedman test shall be used in analyzing non-parametric repeated measures. The main effects of the intervention, time effects, and group x time interaction will be tested using a 2 × 3 two-way repeated measures ANOVA design (group x time), using the Greenhouse-Geisser correction in cases when the sphericity assumption will be violated. The level of significance will be α = 0.05, two-tailed, using Bonferroni adjustment for multiple comparisons. In addition, a repeated measures proportional odds logistic regression model using a generalized estimating equation (GEE) will be applied, assessing the intervention’s effect on CPD treated as an ordinal variable. The GEE model, computed in R using the `repolr` package (122), will contain robust variance estimators that take into account within-subject correlations (**Table 2**).

**Table 2 T2:** Summary of statistical methods and outcomes.

Outcome variable	Domain	Statistical method	Software
Self-efficacy, craving, psychiatric scores	Psychobehavioural	Repeated measures ANOVA, t-tests, Friedman test	SPSS
Cigarettes per day (ordinal)	Psychobehavioural	GEE (Proportional odds model)	R (repolr)
Bacterial diversity indices	Microbiome	Kruskal-Wallis, ANOSIM, db-RDA	R, QIIME
Taxonomic composition	Microbiome	MaAsLin2, ANCOM, LEfSe	QIIME2, R
Metabolite concentrations	Metabolic	PCA, O-PLS-DA, correlation analyses	NMR tools, R
Cross-domain associations	Combined (exploratory)	Correlation and regression	R

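### Section 4.7.1 powers one uncorrected two-wave test and wrongly says machine learning will offset the multiplicity corrections; at the protocol's own cited effect, about 0.90 power covers one test only

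*Protocol article*

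**What the plan says.** All references are to the protocol article.

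- **Section 4.7.1 (Power calculation).** The G*Power calculation is "for a mixed-design ANOVA with one interaction between group (2 groups) and assessments (2 repeated measurements"). It is "set rather conservatively for a medium effect size (Cohen’s F = 0.25"), with "a statistical Power (1-β) of 0.9", "a α of 0.05", a correlation of 0.5 and a nonsphericity correction of 1. The reported result is at least 46 subjects per group and a critical F of 4.06. N is set at 100 to allow for about 10% attrition.
- **Same section, evidence for the effect size.** The pilot self-efficacy result "showed a medium-to-strong effect (η_p_^2^ = .11; converted to Cohen’s d ≈.70"). A metabolite difference between smokers and former smokers is put at d of about 0.73.
- **Same section, multiplicity.** It says that the many variables, mostly biological, will probably need statistical correction, and continues: "this will also be compensated by statistical methods exceeding classical linear approaches, namely machine learning feature detection and modelling methods".
- **Section 4.7.3, omics data.** "Thus, controlling for multiple testing is a must; False Discovery Rate corrections will be based on statistical recommendations". The number of tests is not given.
- **Section 4.7.4, psychological outcomes.** These are tested in a 2 × 3 repeated measures ANOVA. "The level of significance will be α = 0.05, two-tailed, using Bonferroni adjustment for multiple comparisons". The family over which Bonferroni runs is not given. Table 2 puts self-efficacy, craving and psychiatric scores in one row.

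**The concern.** The compensation clause makes a claim about what the design can deliver, and the claim is wrong. A correction lowers the level at which each arm comparison is tested, and the lost power comes back only through more information or a larger effect. Feature selection on the same participants supplies neither. It adds a selection step that needs its own error control or held-out data.

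The clause also takes the place of a statement of what the 0.90 refers to. Section 4.7.1 names no outcome for the powered test and no corrected level, and describes the effect size as conservative. A reader may take 0.90 as the power for craving, symptoms and biomarkers alike. A null result there could then be over-read as evidence of no effect, and machine-selected metabolites or taxa could be given more weight than they have earned.

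**Working it through.** **Inputs from section 4.7.1.** f = 0.25, alpha = 0.05, power 0.90, correlation ρ = 0.5, nonsphericity ε = 1, two groups, m = 2 waves; N = 100 less 10% leaves 90 analysed. The cited effects are d = 0.70 and 0.73. **Assumptions:** the cited d is read as the arm difference in change, in SD units, and Bonferroni is modelled as 0.05/k. The family sizes k are illustrative; the article gives none.

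**Step 1. Reproduce the plan's figure.** Under the G*Power default for a within-between interaction, λ = f²·N·m/(1 − ρ), with df = (1, N − 2).

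- N = 46 in total: λ = 0.0625 × 46 × 2/0.5 = 11.5; df (1, 44); critical F = 4.06; power 0.912.
- N = 92 in total: λ = 0.0625 × 92 × 2/0.5 = 23.0; df (1, 90); critical F = 3.95; power 0.997.

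The printed critical F of 4.06 belongs to 46 subjects in total (23 per group), not 46 per group. Ignoring the correlation does not rescue the pair of figures: it gives 88 in total (44 per group) with critical F 3.95. Treating f as the SPSS-type partial effect gives 174 in total.

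**Step 2. What f = 0.25 means as a difference.** For a difference d in change with equal arms, λ = (N/4)·d². With ρ = 0.5 the SD of change equals the SD at one wave. Setting the two expressions equal: 0.0625 × N × 4 = (N/4)·d², so d² = 1 and d = 1.0. This exceeds both 0.70 and 0.73.

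**Step 3. Power with 90 analysed, df (1, 88).** For f = 0.25, λ = 22.5. For d = 0.70, λ = 22.5 × 0.49 = 11.0.

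| Bonferroni tests k | f = 0.25 as entered | d = 0.70 |
|---|---|---|
| 1 | 0.997 | 0.907 |
| 3 | 0.988 | 0.808 |
| 5 | 0.981 | 0.752 |
| 16 | 0.953 | 0.611 |

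With f = 0.25, power remains at or above 0.90 up to k = 54. At d = 0.73 the one-test power is 0.93.

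**Step 4. Effect detectable with 0.90 power, 90 analysed.** Solving for d gives about 0.69 for one test, 0.79 for three and 0.83 for five.

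**The case against.** The strongest reply is that the protocol's own inputs leave ample reserve. With f = 0.25 and 90 analysed, 0.90 is exceeded for any plausible psychological family, and the three-wave interaction at the same nominal f has power above 0.999. A reader might infer from the uncorrected alpha that the stated power fails for the tests the trial will run. On the entered inputs, that inference is not supported. It becomes true at the smaller effects that the protocol itself cites, or for large omics families whose size is not stated.

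Three further points stand in part.

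- **Scope of Bonferroni.** The sentence in section 4.7.4 may mean only post hoc pairwise comparisons after the ANOVA. The interaction would then be tested at 0.05, as powered. The text does not settle this, so the family sizes above remain assumptions.
- **Omics.** FDR is less strict than Bonferroni, the feature count is unknown, and the d of 0.73 is a cross-sectional difference rather than a randomised difference in change. No definite power figure for the omics tests can be drawn from the article.
- **Exploratory aim.** Section 2 calls the work largely exploratory, and section 4.7.3 keeps multiplicity control mandatory. Machine learning is therefore not offered as a replacement for FDR. It would go too far to infer that the trial plans to report features that fail FDR.

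None of this makes the compensation clause correct, and none of it reconciles 46 per group with a critical F of 4.06.

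**Conclusion.** The point holds in a limited form. The compensation clause is wrong and should go. The effect size is not conservative under the G*Power default: it corresponds to a 1.0 SD difference in change, against cited values of 0.70 and 0.73. With 90 analysed and d = 0.70 read as the arm difference in change, about 0.90 power covers one test at 0.05 and falls to 0.81 with three Bonferroni tests and 0.75 with five. The reserve seen at f = 0.25 depends on an effect larger than either cited d. Separately, the sample-size statement contradicts itself, since a critical F of 4.06 goes with 46 in total and 92 would give 3.95. The results rest on the default effect-size definition, ρ = 0.5 and assumed family sizes. This should be corrected, but it does not show that the trial is too small.

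**What to change.** In section 4.7.1:

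1. Delete the clause saying that machine learning compensates for the corrections.
2. Correct the per-group versus total figure with its critical F, and state which effect-size definition was used.
3. State that power of about 0.90, at d of about 0.70 with 90 analysed, applies to one named test at alpha 0.05. An example is the self-efficacy group-by-time effect from baseline to week 6, the outcome that supplied the pilot effect.
4. Print the effect detectable with 0.90 power after correction: d of about 0.69 for one test, 0.79 for three and 0.83 for five.
5. Say that machine-learning results will be reported as hypothesis-generating, with cross-validated performance.

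Testing craving after self-efficacy in a fixed sequence is an option for the investigators and not part of this correction.

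The cost is rewording and a rerun of the power calculation, with no extra participants or procedures. The drawback is that the stated power will look less favourable for every comparison except the named one.

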#### Diet

4.7.2

Nutritional variables will be a highly relevant source of variance in the study, particularly for metabolome and microbiome parameters. Food compounds, energy and nutrient intake will therefore be analysed from food frequency data by the nutritional software nut.s ^®^v1.32.95 (110). Nutrient intake will be adjusted for total energy intake, and nutrients with excessive missings will be excluded.

It appears inadequate to consider dietal factors merely as control variables, as nicotine is known to interact strongly with regulation of appetite and satiety, and smoking cessation usually goes along with a weight-gain (111). Nutritional variables are therefore candidate mediator or explanatory variables, and it is important to quantify how much of the group effects will be explained by energy intake and nutrients. For this purpose, the variance explained by nutrition will be quantified via Partial distance-based redundancy analysis (db-RDA) and/or PERMANOVA (for both microbial beta diversity and metabolite distances). Variance will be decomposed by stepwise separation of variance explained by group, variance explained by nutritional variables (energy, nutrients, selected compounds), control variables (see below), and shared variance.

Additional adjustment analyses will be performed in candidate biomarkers of smoking cessation group effects emerging from metabolome and microbiome analyses (at the level of metabolites, or specific bacterial taxa). Linear mixed effects models (lme4 package in R (112)) will be iteratively tested (total effect vs. nutrition-adjusted models) for shrinked coefficients of group effects for this purpose.

#### Controlling for potentially confounding variables, and multiple testing

4.7.3

Proper analysis of the research questions in the SUD sample will be hampered by several sources of variance, such as diet, psychiatric diagnoses, medications, and history of substance misuse. These variables will be held constant as control variables.

Psychiatric comorbidity is highly present in the population. Psychiatric symptom burden and classes of psychiatric diagnoses are associated with systematic metabolic and microbiome profiles (72, 113, 114). Classes of psychiatric secondary diagnoses (mood, anxiety, psychotic, and neurodevelopmental disorders) will therefore be considered as covariates. Intake of psychotropic medications are respectively frequent. The literature shows reciprocal interactions between psychotropic medications and gut microbiota (115), and metabolic patterns in response to treatment (116, 117). Type of medication class intake (antipsychotics, antidepressants, antianxiety drugs, anticonvulsants/mood stabilisers, opioid substitution) will be considered as covariates. Length and consumption patterns from SUD history will also enter covariate analysis (with regard to substances – primarily consumed substances vs. polytoxicomania). These covariates will be entered in Multi-omics factor analysis (MOFA) in direct joint modeling (118) to ensure that observed microbiome–metabolome–psychological associations are not driven by covariate effects. For the microbiome domain, intervention vs. control group comparisons regarding microbial abundance and composition will be performed with Analysis of Compositions of Microbiomes with Bias Correction (ANCOM-BC), a package which allows for continuous and categorical covariate adjustment within a linear regression framework, and was designed to analyze longitudinal data (119).

Metabolome and microbiome studies involve the examination and statistical testing of a multitude of variables. Thus, controlling for multiple testing is a must; False Discovery Rate corrections will be based on statistical recommendations promoting flexible algorithms within the R package FDRestimation (120).

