#### Oxidative stress, lipid and inflammatory pathways

1.8.2

A multi-omics study compared metabolite levels between cigarette smokers, e-vapers, former smokers and never smokers (27). Metabolic concentrations showed distinct smoking dose-dependent distributions of elevated inflammation markers and pathways. In smokers, apart from nicotine and its downstream metabolites, metabolites derived from toxicants (e.g. p-cresol sulfate), increased metabolites of oxidative stress and detoxification pathways (pathways of gluthatione conjugation) were found. Lower caroten-diol levels indicated oxidative depletion of antioxidants. Oxidative stress responses are known to be associated with exacerbation of withdrawal symptoms and enhance reward seeking (63). Lipidomics analyses revealed increased concentrations in oxidized derivatives of polyunsaturated fatty acids (PUFAs). More precisely, eicosanoid derivates such as 14,15DHET or 9-HODE, known to be involved in inflammatory signaling, were elevated. Circulating CRP and haptoglobin were also increased, reflecting chronic inflammation in smokers. Strongly elevated levels of N-acetylputrescine were also observed, a metabolite related to polyamine metabolism and influencing cell proliferation, immune function, and stress responses (27). Similar and confirmatory patterns of increased inflammatory activation with elevated CRP and interleukin-6, and lipid profiles (cholesterol, triglycerides, LDL) in smokers vs. controls were recently published (64).

Activation of oxidative and cell stress, and lipid inflammatory pathways are linked in complex ways to reward circuitry. There is evidence for associations with blunted reward and increased propensity for immediate gratification via dopamine pathways in the nucleus accumbens and medial prefrontal cortex, but also increased negative affectivity, learned helplessness, and proneness for depression (65, 66).

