#### Psychobehavioural variables – psychometric measures

4.4.1

In addition to anamnestic data, the following previously validated instruments showing good psychometric properties will be applied:

Self-efficacy: The Self-Efficacy Scale (SWE (100)) is a self-report instrument for measuring general optimistic self-confidence. It consists of 10 items and measures optimistic competence expectancy, i.e., confidence in solving difficult situations with one’s own abilities.

General substance related craving: The MaCS (Mannheim Craving Scale (101)) is an instrument for measuring substance related craving. It consists of 12 items and four additional items and is rated on a 5-point Likert scale.

Tobacco dependence: The Fagerström Test for Cigarette Dependence (formerly Fagerström Test for Nicotine Dependence; FTND (102)) is a self-assessment instrument measuring tobacco dependence intensity. It consists of 6 categorically scaled items that assess the number of smoked cigarettes per day (CPD), compulsive use, and dependence intensity.

Psychiatric Symptoms: For the evaluation of psychopathology, the ICD-10 Symptom Rating (ISR (103)) questionnaire was utilized. In accordance with the ICD-10, this self-assessment questionnaire, comprising 30 items, is designed to comprehensively assess the status and severity of mental disturbances. Symptoms of the six symptomatic patterns – depressive, anxiety, obsessive-compulsive, eating disorders, somatoform syndrome, and post-traumatic stress disorder – are assessed.

Primary Affects: The German version of the Brief Affective Neuroscience Personality Scales including a LUST Scale (BANPS–GL (104)) is a self-report questionnaire to measure all seven primary affects proposed by Jaak Panksepp (105) as personality traits.

Smoking behaviour: As previously in the pilot study, participants will be asked regarding their daily smoked cigarettes in the last two weeks (interval scaled). A second, dichotomous single-item question will assess if participants have been completely abstinent from tobacco smoking in the last two weeks.

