
For beta diversity, db-RDA will be performed on Bray-Curtis, Jaccard, and UniFrac distance matrices (weighted and unweighted) to compare the structural similarities between groups’ microbiomes. Beta diversity indices will be visualized with PCoA plots using Bray-Curtis and Jaccard dissimilarities. The Firmicutes/Bacteroidetes (F/B) ratio will be calculated from the rarefied feature table. Using this, MaAsLin2 will be used to detect differentially abundant taxa and further test associations with variables of interest such as cigarettes per day or metabolic markers (126). Identifications of microbial biomarkers will then be done applying LeFSe both in longitudinal and cross-sectional comparisons. This will be furthered to detect significant differences between groups in the microbial taxonomic abundance using the Analysis of Composition of Microbiomes’ ANCOM-BC implemented within QIIME2 (119).

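### The covariate set in section 4.7.3, meant to protect the exploratory cross-domain associations, omits baseline smoking dose, which the trial already collects.

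*Protocol article*

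**What the plan says.** Section 4.7.3 of the protocol article lists what may hamper the analysis, "such as diet, psychiatric diagnoses, medications, and history of substance misuse", and adds: "These variables will be held constant as control variables". It then details the set: four classes of secondary psychiatric diagnosis, five medication classes, and substance history. On the last it says: "Length and consumption patterns from SUD history will also enter covariate analysis", with primary substance set against polytoxicomania. These covariates enter the multi-omics factor analysis (MOFA) "to ensure that observed microbiome–metabolome–psychological associations are not driven by covariate effects". Section 8 adds sex.

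Smoking intensity is collected twice. Section 4.4.1 says that "participants will be asked regarding their daily smoked cigarettes in the last two weeks (interval scaled"), and that the Fagerström items "assess the number of smoked cigarettes per day (CPD), compulsive use, and dependence intensity". Section 4.2 places the questionnaires before random allocation, so a pre-randomisation value exists.

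The article uses smoking quantity or history in three other ways. Cigarettes per day is an outcome in the GEE model (4.7.4). It is also one side of a MaAsLin2 search for "associations with variables of interest such as cigarettes per day or metabolic markers" (4.7.5). History of smoking is a target for microbial markers (2.1.3). Nowhere is smoking dose named as an adjustment variable.

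**The concern.** The covariate set has a stated job: to keep cross-domain associations from being produced by a third variable. The article itself supplies the material for smoking dose to be such a variable.

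- **Biology.** On the cited multi-omics study, section 1.8.2 says: "Metabolic concentrations showed distinct smoking dose-dependent distributions of elevated inflammation markers and pathways". Sections 1.8.3 and 1.8.4 report lower short-chain fatty acids and lower choline in smokers.
- **Psychology.** Section 1.3 says that smoking worsens mood and causes anxiety and stress. Section 1.8.1 links chronic smoking to depressed mood, agitation and anxiety.

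Sections 2.1.2 and 2.1.3 plan to look for metabolic and microbial correlates of primary emotions and psychiatric symptoms, and 2.1.3 also seeks microbial markers of craving. Table 2 assigns correlation and regression to the cross-domain associations. If heavier smokers have both a shifted metabolite and a worse mood or craving score, the two will correlate even when neither affects the other. None of the listed covariates would remove that. Substance history coded as primary substance versus polytoxicomania does not measure cigarette dose. Because every participant must want to quit smoking (4.5), what varies between participants is the amount smoked rather than whether they smoke.

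**Working it through.** The article states no figure for this point, so there is none to reproduce. The check has two parts.

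**1. Is smoking dose anywhere an adjuster?**

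| Place | Role of smoking quantity or history |
|---|---|
| 4.7.3, covariates | not named |
| 8, added covariate | sex only |
| 4.7.4, GEE | cigarettes per day as outcome |
| 4.7.5, MaAsLin2 | cigarettes per day as variable of interest for taxa |
| 2.1.3 | smoking history as target of marker search |

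None of these uses adjusts a metabolite–craving, metabolite–emotion or taxon–symptom association for dose.

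**2. How large could the effect be?**

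Inputs: N = 100 (4.1) and, after about 10% attrition (4.7.1), n = 90. The correlations of dose with the biological marker (a) and with the psychological score (b) are assumptions, set from 0.2 to 0.5.

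If marker and score are linked only through dose, their marginal correlation is

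r = a × b.

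Their partial correlation given dose is (r − ab) / √[(1 − a²)(1 − b²)] = 0.

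The chance of p < 0.05 (two-sided), by the Fisher approximation, with z = atanh(r) × √(n − 3), is

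1 − Φ(1.96 − z) + Φ(−1.96 − z).

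Worked case, a = b = 0.5 and n = 100: r = 0.25; z = 0.2554 × √97 = 2.516; probability = 1 − Φ(−0.556) + Φ(−4.476) ≈ 0.71.

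| a | b | spurious r | p < 0.05 at n = 100 | at n = 90 |
|---|---|---|---|---|
| 0.2 | 0.2 | 0.04 | 7% | 7% |
| 0.3 | 0.3 | 0.09 | 14% | 13% |
| 0.4 | 0.3 | 0.12 | 22% | 20% |
| 0.4 | 0.4 | 0.16 | 36% | 33% |
| 0.5 | 0.5 | 0.25 | 71% | 66% |

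A simulation of 20,000 data sets of N = 100 agrees where it overlaps: 14.8% (0.3, 0.3), 22.5% (0.4, 0.3), 36.1% (0.4, 0.4) and 71.8% (0.5, 0.5). With a well-measured dose in the model, the rate returns to about 5%. Self-reported cigarettes per day measures dose with error, so adjustment would remove most of the effect rather than all of it.

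**The case against.** **The list is open and the analysis plan is not shown.** The sources of variance are introduced as examples, and sex appears only in section 8, so the list is not closed. A missing covariate is often settled in the analysis plan. This stands in part: nothing shows that the final analysis will ignore dose. But 4.7.3 goes on to name specific covariates, commits those to MOFA and states their purpose. As written, the set leaves an evident gap for that purpose.

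**Smoking may be an effect, not a cause.** Section 1.8.3 reports that low Actinobacteria may increase smoking. Sections 1.7 and 1.8.1 treat negative affect as a motive for substance use. If marker and affect both drive smoking, conditioning on dose can create an association or remove part of a real one. This stands, and it rules out treating adjustment as cost-free or the adjusted result as the only correct one.

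**The size is assumed.** No within-smoker correlations are given. The dose dependence in 1.8.2 comes from a study that also included e-vapers, former smokers and never smokers. Participants here all want to quit smoking, so the range of exposure may be narrower. Dose dependence on the psychological side is an inference. At 0.2 on each side the excess is only about two percentage points. This stands.

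**The associations are exploratory and FDR-controlled.** It is true that no confirmatory claim rests on them. FDR control limits chance findings but does not remove confounding. It does mean that the percentages above are not the plan's own error rates.

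**The randomised comparisons.** A reader might infer that the arm comparisons are also confounded. They are not: baseline dose is balanced in expectation, and the pre/post design absorbs most stable differences between participants.

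**Conclusion.** The point holds for the observational, exploratory associations: MOFA, the MaAsLin2 associations, and the cross-domain correlations and regressions. Under the covariates that 4.7.3 names, these could partly reflect how much a participant smokes. Under assumed dose correlations of 0.2 to 0.5 with each side, the spurious correlation is 0.04 to 0.25, nominally significant in about 7% to 71% of single uncorrected tests at N = 100. These figures assume that dose is the only link and is a common cause. The true size cannot be derived from the document.

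Two stronger readings are not supported. One is that false links will be declared at these rates: the correlations are assumed, and the planned analyses are exploratory and FDR-corrected. The other is that the intervention effect on metabolites or taxa is biased: in those comparisons a baseline dose term offers at most a small gain in precision and cover for chance imbalance.

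**What to change.** In 4.7.3, add one baseline smoking-dose measure to the covariates for MOFA, MaAsLin2 and the cross-domain regressions. Use either cigarettes per day or the Fagerström score, not both, because the Fagerström items already contain cigarettes per day. Where MaAsLin2 has cigarettes per day as the variable of interest, no separate dose term is needed.

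For associations that use post-intervention data, include arm as well. Do not adjust for smoking after randomisation, since it lies on the path from intervention to outcome. Baseline dose alone does not fully protect these post-intervention associations, and the report should say so.

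Report each cross-domain association with and without the dose term, and state that the two may differ either because dose confounds or because the marker or affect influences smoking. In ANCOM-BC and the other arm comparisons the term is optional.

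Cost: a sentence or two in the plan, no new data, and one degree of freedom per model. That is small, but it comes on top of an already long covariate list for 100 participants. The remaining downside is over-adjustment if smoking is a consequence of the marker or of affect; showing both sets of results makes that visible.
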